#### Follow-up.

Each person will receive a follow-up phone call after the test has been completed. The participant will be asked structured questions regarding the testing procedure:

“Which sample did you collect first?” (bulk/swab). This will help to validate the timing of sample collection, ensuring that samples that were collected close together (e.g., the participant records the same collection time for the swab and container) in time can be ordered.“Did you experience an adverse event during or after collecting the swab sample? (yes/no). If so, what was the nature of the event?” (qualitative). The adverse event will then be classified according to classification definitions described in ‘adverse event reporting and harms’.“Which test did you prefer?” (bulk/swab). “Why?” (qualitative)

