### Data collection and management

Laboratory diagnostics will provide the majority of the outcomes using established testing methods. Pathologists will provide the diagnosis for samples. We will be collecting information about demographics, symptomatology, setting it was collected in, type of collect (self-collect vs clinician collect), and two patient reported outcomes by firstly asking the patient if they had an adverse event during or after the testing, and the nature of the event if present. Secondly, we will ask the patient which test they preferred and follow-up with why. Data analysis will be conducted by members of the research team.

Participant-level dataset will not be publicly accessible. Statistical code and full protocol will be publicly accessible.

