#### Minimum data requirements.

At a minimum, data collected for each participant should include:

Identifiers (name, address, date of birth, contact details, comorbidities)Recruitment details (date of recruitment, date of consent, proof of consent, date that test packs were posted, symptomatology, duration of symptoms, presence of blood in faeces (if applicable))Sample collection details (where samples were collected (e.g., at home), who collected the sample (e.g., self-collect), date and time each sample was collected, date samples were submitted to pathology lab)Bulk faeces and rectal swab test results (date that lab testing was conducted for each sample, presence of visible faeces for the rectal swab only, positive/negative detection results for each sample)Follow-up information (date of follow-up attempts, which sample was collected first as reported by the participant, rough estimate of time difference between samples collected, adverse event details, preferred sample method)

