#### Secondary outcomes.

We will calculate the number and percentage of participants experiencing at least one adverse event, and the total number of adverse events reported. We will tabulate the distribution of adverse events by severity (mild, moderate, severe) for both the rectal swab and bulk faeces groups. Summarise AEs by expectedness (expected, unexpected) and relatedness (definitely, probably, possibly, unrelated) for each group. We will report the incidence rates of adverse events per 100 participant-days for each group, allowing for comparison over different follow-up periods. We will use chi-square tests or Fisher’s exact tests to compare the incidence rates of adverse events between the rectal swab and bulk faeces groups. We will use ordinal logistic regression to analyse the severity of adverse events, treating severity as an ordinal outcome. We will include group (rectal swab vs. bulk faeces) as the main predictor and adjust for potential confounders (e.g., age, gender, mode of testing, and location of testing).

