#### Decision rules.

Stopping for Safety: Predefined criteria for stopping the trial if a significant safety concern are identified; for instance, if the incidence of severe adverse events is above what is expected.Stopping for Efficacy: Criteria for stopping the trial early if rectal swabs show clear and overwhelming evidence of inferiority, based on predefined statistical thresholds and thus it is futile to continue. A cutoff of 0.35 difference in accuracy for inferiority with an alpha of 0.05 at interim analyses will be used to support decisions on continuing, modifying, or stopping the trial. As this is a diagnostic test trial, the decision to stop the trial must be multifactorial in nature and made by the Trial Steering Committee.

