SeverityMild: Adverse events that are easily tolerated and do not interfere with daily activities. These could include minor discomfort or irritation at the site of the rectal swab.Moderate: Events that cause some interference with daily activities but are not dangerous. Examples may include moderate pain, cramping, or a temporary increase in bowel movement frequency.Severe: Events that significantly interfere with daily activities or pose a risk to health. Severe adverse events might involve intense pain, bleeding, or infection requiring medical intervention.ExpectednessExpected Adverse Events: These are events that are known to occur based on previous studies or the nature of the procedures. For rectal swabs, this could include expected mild discomfort or minor bleeding.Unexpected Adverse Events: Events that are not anticipated based on prior knowledge. Unexpected events could be severe allergic reactions, systemic infections, or unusual gastrointestinal symptoms.Relatedness to ProcedureDefinitely Related: There is a clear, direct link between the adverse event and the rectal swab procedure. An example is rectal bleeding immediately following the swab.Probably Related: There is a reasonable likelihood that the event is related to the procedure, but other factors could be involved. For instance, discomfort that occurs after the procedure and subsides soon afterward.Possibly Related: The event could be related to the procedure but could also be attributed to other causes. This might include abdominal pain occurring days after the procedure.Unrelated: The event has no apparent connection to the procedure. An example is an adverse event like a headache, which is likely due to other factors.4. Type of Adverse EventLocal Adverse Events: These are events occurring at the site of the rectal swab. They might include irritation, redness, or bleeding.Systemic Adverse Events: Events affecting the body beyond the local site, such as fever, nausea, or generalised infection.Procedure-Related Adverse Events: Specific to the process of specimen collection, like discomfort during the swab insertion or difficulties with the bulk faeces collection method.Non-Procedure-Related Adverse Events: Unrelated to the procedure itself, such as a common cold or unrelated illness occurring during the trial period.

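### The scripted follow-up question does not collect what the severity and relatedness grades depend on

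*Protocol article*

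**What the plan says.** The Follow-up section of the protocol article prints the structured call questions. The one on harms reads: "Did you experience an adverse event during or after collecting the swab sample? (yes/no). If so, what was the nature of the event". The second half is marked as qualitative. The next sentence begins "The adverse event will then be classified according to classification definitions described in" and points to the adverse event definitions. Data collection and management describes the same two pieces of information: "firstly asking the patient if they had an adverse event during or after the testing, and the nature of the event if present". Minimum data requirements lists, among the follow-up items, "rough estimate of time difference between samples collected, adverse event details, preferred sample method".

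The Adverse event reporting section then sets out the grades. Mild events are tolerated easily and leave daily life undisturbed. Moderate events are "Events that cause some interference with daily activities but are not dangerous". Severe events either disrupt activities significantly or put health at risk. Relatedness runs from definite to unrelated according to the strength of the causal link. Each level has an example; the one for probably related is "For instance, discomfort that occurs after the procedure and subsides soon afterward".

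Under Secondary outcomes, events are tabulated by severity, expectedness and relatedness for the rectal swab and bulk faeces groups, and "We will use ordinal logistic regression to analyse the severity of adverse events, treating severity as an ordinal outcome". Objectives of interim analysis has severity and relatedness reviewed during the trial. Decision rules gives as an example of a safety criterion "if the incidence of severe adverse events is above what is expected".

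**The concern.** The article fixes the question, says that classification follows from it, and defines the classes. The question and the class definitions do not match. Whoever grades the event is given its occurrence and a free description. The grades turn largely on its effect on daily activities, and the relatedness examples turn on when it began and how soon it settled.

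If callers and sites fill that gap in their own way, the severity variable will partly reflect what each participant volunteered or each caller chose to probe. That variable is the outcome of a planned regression. The relatedness grade also matters beyond its own table, because the article counts probably and definitely related events as adverse reactions.

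**Working it through.** No arithmetic applies: the point depends on no sample size, rate or margin. The check sets the items collected against the items the definitions need.

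1. **What the call yields.** It yields a yes or no, an open description, and the loose timing implied by asking about events during or after the swab. It concerns the swab only.

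2. **Mild versus moderate.** The definitions differ on whether daily activities were affected. No named item asks this. The description of the event does not reliably stand in for it: the article's own examples place discomfort or pain at all three grades, distinguished by an adjective (minor, moderate, intense). A participant who says only that it hurt, or that there was cramping, has not supplied the grade.

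3. **Severe.** There are two routes: significant disruption, or a risk to health. The second can often be recognised from a description, infection being the clearest case. Whether medical care was needed, which features in the severe examples, is not asked. The gap is real here but smaller than in step 2.

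4. **Relatedness.** The definitions rest on causal link, and timing enters only through the examples. Those examples are what a grader would use to tell the levels apart: bleeding straight after the swab (definite), discomfort that soon passes (probable), abdominal pain some days later (possible). A question about events during or after the swab does not separate these. The date and time of each sample are in the minimum data, so the reference point exists, but the event's onset and end are not named. This matters because participants include people presenting with diarrhoea. Two of the moderate examples, cramping and more frequent bowel motions, could equally come from the illness that led to enrolment.

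5. **The minimum data list.** The adverse event entry is general. It could hold impact and timing, but it names neither. In the same line the interval between the two samples is listed as a separate item.

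6. **The comparison.** In the ordinal model the main predictor is rectal swab versus bulk faeces. The printed question asks about the swab alone. Data collection and management speaks of the testing in general, which could cover both collections, but the call script does not.

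Result: mild versus moderate is the weakest boundary, severe grading and relatedness are partly supported, and the bulk faeces side has no scripted question at all.

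**The case against.** The strongest reply is that the script is not the whole record. The nature question is open-ended, so a participant can describe intensity, impact and timing. The minimum data call for adverse event details beyond a yes or no. They also include the time difference between samples, which is not among the scripted questions either, so the call evidently gathers more than is printed. The article condenses a fuller protocol, and Missing data says that minimum requirements are defined in the data collection platform, where coded fields may exist.

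Much of this stands, and it limits the point. It does not remove it, because the article does not leave the instrument to another document: it prints the question, repeats its content in a second section and states that classification follows. An open question may draw out impact and timing, but not consistently across callers and sites.

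Four stronger readings are tempting and are not supported.

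- **That the safety stop rests on guesses.** Severe-event incidence is given only as an instance, the decision is described as multifactorial and belongs to the Trial Steering Committee, and severe events are the ones a description is most likely to reveal.
- **That the missing information is lost for good.** Contact details are held until the data are verified and cleaned, so a call-back is possible.
- **That relatedness is defined by timing.** It is defined by causal link; timing only illustrates it.
- **That the technical term leads lay participants to under-report mild events.** This is plausible, but nothing in the article shows it, and participants are told beforehand about discomfort, pain, bleeding and infection.

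**Conclusion.** The point holds as a mismatch between the stated follow-up question and the stated grading definitions. As scripted, mild versus moderate cannot be assigned consistently. Severe grading and relatedness are affected less. The consequence falls on the severity and relatedness tables and on the ordinal regression, which belong to a secondary outcome; the primary accuracy results are untouched.

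No numerical size is offered. The article gives no expected adverse event rate and nothing on how often a grade would be wrong, so any figure would only restate an assumption.

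The conclusion assumes that the call follows the printed wording and that the general adverse event entry carries no further prompts. If the data collection platform already has coded fields for impact, care and timing, what remains is to say so in the article and to extend the questions to the bulk faeces collection. The change is worth making: it is cheap, and it gives the planned analysis the variable it presupposes.

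**What to change.** In the Follow-up script, after any yes, add coded items:

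- interference with daily activities: none, some or significant;
- whether medical care was needed;
- when the event started and stopped, relative to collection.

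List these under the adverse event entry in Minimum data requirements, and state that severity and relatedness are assigned from them together with the description.

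Ask the same opening question and follow-up items about the bulk faeces collection, because Secondary outcomes compares the two. The definition of a definitely related event names only the rectal swab, so it would need to cover either collection.

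Plain-language wording in place of the term adverse event is optional. Its downside is that it may raise the reported rate of mild events, so it should be used from the first participant or not at all.

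The cost is about a minute on a call that is already made, longer now that two collections are covered, plus a form edit and a minor ethics notification. No clinical rule changes.

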### Outcomes

Primary Outcomes: Assess sensitivity, specificity, positive and negative predictive value, positive and negative agreement, accuracy, and receiver operating curves (at various CT value cutoffs), to determine the efficacy the new rectal swab approach.

Secondary outcomes: Acceptability of the rectal swabs in comparison to the gold standard of bulk faeces testing. This will be measured by asking participants which sampling method they preferred, and collecting information from participants in relation to any adverse events that may have occurred.

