#### Missing data.

To minimise occurrences of missing data, the data collection tool will be designed in a clear and easy-to-operate format. Any members of the research team who may be responsible for data collection and data input will be familiarised with data collection/storage tools and processes, which will ultimately reduce occurrences of missing data due to an avoidable error. Minimum data requirements are defined within the data collection platform to ensure instances of missing data are easily identifiable and can be followed up promptly (e.g., missing symptomatology details).

Data relevant to consent, participant identifiers and dual samples must be reported at the bare minimum. We will require each site to monitor and report missing data every 6 months. If a participant withdraws from the study after providing consent, the reason for withdrawal will be recorded and taken into account in data analysis and interpretation stages. Non-critical missing data will be managed via sensitivity analyses, and if amenable, multiple imputation will be used. In the event that a participant does not return the swab (critical data), that participant will be contacted to check if they wish to withdraw from the study. If the individual wishes to remain part of the study, they will be supported to provide the additional sample (e.g., required sample kit will be provided again if necessary). Participants will be encouraged to supply the bulk faeces sample at a minimum to complete routine clinical or public health care. If the participant withdraws from the study, or is unable to be contacted, the participant’s data will be omitted.

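### The follow-up preference question lists only bulk or swab as answers; adding 'no preference' would be a cheap improvement to the acceptability outcome

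*Protocol article*

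**What the plan says.** Under Outcomes, the protocol article makes acceptability of the swab relative to bulk faeces a secondary outcome and states how: "This will be measured by asking participants which sampling method they preferred, and collecting information from participants in relation to any adverse events".

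Under Follow-up, the question is given with its two answers, "Which test did you prefer?” (bulk/swab", and an open question on the reason comes after it. Data collection and management repeats the pair without listing answers: "Secondly, we will ask the patient which test they preferred and follow-up with why". Minimum data requirements names the field among the follow-up items, "adverse event details, preferred sample method", and gives no coding. None of these four sections lists an answer for a participant who has no preference.

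The Secondary outcomes part of Statistical methods deals only with adverse events. It sets no scoring rule, test or threshold for preference. Missing data states a general rule: "Non-critical missing data will be managed via sensitivity analyses, and if amenable, multiple imputation will be used".

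**The concern.** Every participant is asked to provide both samples, so finding them equally acceptable (or equally unpleasant) is a plausible answer. With two listed answers such a person has no code. Either a side is chosen, by the participant or by the caller, or the item stays blank. The published preference percentages would then depend partly on how callers handle indifference.

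The item matters because it is the only listed follow-up question that compares the acceptability of the two methods; the adverse-event question in the same list asks only about collecting the swab. The Introduction says the aim is for swabs to take the place of bulk faeces in daily practice. For that aim, people who do not mind which sample they give are informative, and a two-answer item merges them with people who hold a definite view.

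**Working it through.** The article states no expected preference split, test or threshold, so there is no figure of its own to reproduce. What can be worked out is how far a two-answer result can depart from a three-answer one.

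**Inputs**
- Listed answers: bulk and swab (Follow-up).
- u, the share of participants with no preference: not in the article; assumed 5% to 30%.
- r, the swab share among those with a preference: not in the article; assumed 70%.
- f, the fraction of indifferent participants recorded as swab when a side is chosen: unknown, 0 to 1.

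**Formulas**
- Swab share with three answers: S = (1 − u)r.
- Swab share with two answers, side chosen: S + fu. The excess is fu, so it lies between 0 and u.
- Swab share with two answers, indifferent left out of numerator and denominator: S/(1 − u) = r. The excess is r − (1 − u)r = ur, again between 0 and u.
- Swab minus bulk with three answers: D = (1 − u)(2r − 1). With a side chosen: D + u(2f − 1), which equals D when f = 1/2.

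**Results at r = 70%**

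| u | Three-answer swab share | Two-answer range (f = 0 to 1) | Even split | Left out | D |
|---|---|---|---|---|---|
| 5% | 66.5% | 66.5% to 71.5% | 69.0% | 70.0% | 38 points |
| 10% | 63.0% | 63.0% to 73.0% | 68.0% | 70.0% | 36 points |
| 20% | 56.0% | 56.0% to 76.0% | 66.0% | 70.0% | 32 points |
| 30% | 49.0% | 49.0% to 79.0% | 64.0% | 70.0% | 28 points |

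For example, at u = 20%: S = 0.80 × 0.70 = 56%; even split 56 + 10 = 66%; D = 0.80 × 0.40 = 32 points, and after an even split 66 − 34 = 32 points. At u = 0 the two formats agree.

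**What cannot be recovered.** Suppose the two-answer item returns 60% swab and 40% bulk. This fits true shares of 60 / 40 / 0 (swab / bulk / no preference). It fits equally well true shares of 40 / 20 / 40 with the indifferent split evenly: 40 + 20 = 60 and 20 + 20 = 40. The share preferring the swab or having no preference is 60% in the first case and 40 + 40 = 80% in the second. The coded item cannot tell them apart.

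**The case against.** The strongest reply is that forced choice is a legitimate format. It estimates a defined quantity, the share choosing the swab when made to choose, and an even split of the indifferent leaves the swab-minus-bulk difference intact. This stands. A reader might infer that the reported preference will be wrong; the document does not support that, because the indifferent share and the way such people answer are unknown, and no preference figure or threshold is stated that could be in error.

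Second, the item does not stand alone. Adverse-event information is also part of the acceptability outcome, and the open question on reasons gives indifference somewhere to surface. So it would be too strong to say that indifferent participants are certain to be lost. But the open question follows a choice already made, its answers are free text, and no coding rule for them is given. It helps only in part.

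Third, the bracketed answers may be shorthand in a condensed article, with fuller codes in a document not shown. That is possible, and it limits the point to a suggestion. Still, the article does state the answer set, and what is not recorded at the call cannot be restored reliably by a later analysis plan.

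Fourth, a reader might infer that blank answers will be imputed as bulk or swab. The Missing data section only allows imputation where amenable and does not name preference. The risk is possible, not planned.

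**Conclusion.** The point holds as a minor, nearly costless improvement. As listed, the item has no place for participants without a preference. The reported swab share may therefore be overstated by 0 to u points: 0 to 5 at u = 5%, 0 to 30 at u = 30%. These values of u are assumptions; the article gives none, so no single size of error can be claimed. The zero end is reached if nobody is indifferent, or if everyone indifferent is recorded as bulk, in which case the bulk share carries the excess instead.

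What survives even under an even split is that the share with no objection to replacing bulk faeces cannot be separated out reliably. The matter is confined to a descriptive part of a secondary outcome and does not touch the primary accuracy outcomes or the sample size.

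**What to change.** - Add 'no preference' as a third answer in the phone script and in the preferred-method field of the minimum data set.
- Report the swab, bulk and no-preference shares with 95% confidence intervals, over all participants asked.
- Show 'swab or no preference' only as a supplementary figure, read alongside the stated reasons. It should not replace the three shares as the acceptability estimate, because it would also count people who dislike both methods equally.
- State that no-preference answers will not be imputed as bulk or swab.
- Recruitment was expected to start in early 2025. If calls have already been made with two answers, report the two versions of the item separately and screen the earlier reasons for signs of indifference.

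The cost is one answer option in a script and a database field. The downside is that fewer participants will give a definite preference.
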